### 6.1.3 Other study parameters (if applicable)

Not applicable

## 6.2 Randomisation, blinding and treatment allocation

Randomization: 200 patients will be 1:1 randomized over the two different dosing strategies. We will use stratified block randomisation using the computer programme CASTOR ([nl.castoredc.com](http://nl.castoredc.com)). In order to make comparable groups, the stratification will take 1. CYP-based phenotype, 2. drug type (NOR vs.CLOMI vs.IMI), and 3. baseline patient status (inpatient vs. outpatient) into account (in this order). An exception to this randomization protocol is when a patient carries a deviant cytochrome P450 metabolism for both CYP2D6 and CYP2C19 while imipramine is prescribed. In this case, patients will be switched to nortriptyline and randomized accordingly. As the number of stratification variables should be limited to avoid empty cells, we will plan additional statistical adjustments for gender, age and sociocultural differences in case of imbalance between study groups.

## 6.3 Study procedures

The table below shows the procedures according to the research proposal.

|                             | Visit
day
week                                                                           | 1
-7
-1 | 2
0 | 3
7
1 | 4
14
2 | 5
21
3 | 6
28
4 | 7
35
5 | 8
42
6 | 9
49
7 |
|-----------------------------|------------------------------------------------------------------------------------------------|---------------|--------|-------------|--------------|--------------|--------------|--------------|--------------|--------------|
| Procedure            |                                                                                                |               |        |             |              |              |              |              |              |              |
| Informed consent            | x                                                                                              |               |        |             |              |              |              |              |              |              |
| SCID-I                      | x                                                                                              |               |        |             |              |              |              |              |              |              |
| Psychiatric assessments     | x                                                                                              |               |        |             |              |              |              |              |              |              |
| Medical history             | x                                                                                              |               |        |             |              |              |              |              |              |              |
| CYP 450 genotype            | x                                                                                              |               |        |             |              |              |              |              |              |              |
| Laboratories + ECG          | x                                                                                              |               |        |             |              |              |              |              |              |              |
| Plasma for storage          |                                                                                                |               | x      |             |              |              |              |              |              | x            |
| Physical examination        | x                                                                                              |               |        |             |              |              |              |              |              |              |
|                             |                                                                                                |               |        |             |              |              |              |              |              |              |
| SRRS-6 (retardation)        |                                                                                                |               | x      |             |              |              |              |              |              | x            |
| Medication prescribed (TCA) |                                                                                                |               | x      | x           | x            | x            | x            | x            | x            | x            |
| Plasma levels               | 12 hours after first dose and repeated at steady state until primary endpoint has been reached |               |        |             |              |              |              |              |              |              |
| Adverse effects (ASEC)      |                                                                                                |               | x      | x           | x            | x            | x            | x            | x            | x            |
| HAM-D/QIDS                  | x                                                                                              |               | x      | x           | x            | x            | x            | x            | x            | x            |
| EQ5D and SF36               |                                                                                                |               | x      |             | x            |              | x            |              | x            |              |

**Description:**

To maximize generalization of the results we aim to perform the study according to the principles of high standard care for severely depressed patients for whom a tricyclic antidepressant is prescribed. Therefore the baseline investigations include a formal psychiatric assessment which includes SCID-I (Structured Clinical Interview for DSM-IV Axis I: a clinical interview designed to elicit the DSM-IV criteria). Based on the SCID-I we conclude if patients fulfil psychiatric inclusion criteria. Other routine procedures in clinical practice are assessments of Medical history, physical examination and Laboratory investigations (Hb, Ht, Ery's, Leuco's, Diff, Na, K, Ureum, Creat, ASAT, ALAT, LDH, yGTP, Free T4, TSH) and ECG (only when indicated), examination physical examination are all in agreement with the procedures that should be offered in high standard clinical care and cannot considered to be a extra burden to the patients. Based on these investigations we can decide if patients fulfil inclusion criteria.

Repeated administration of scales for the measurements of the depressive symptoms (HAM-D/QIDS), adverse events (ASEC and FIBSER) and the measurements of TCA plasma levels are also in agreement with careful common clinical practice.

To answer the main research question, CYP450 genotyping will take place (blood withdrawal will take place together with that for laboratory investigations). At baseline and after 7 weeks we will take plasma for storage and the SRRS-6 retardation scale (Widlöcher et al. 1989; observational scale scored by the researcher), will be administrated. Twelve hours after the first TCA dose an early plasma TCA level will be measured. Other interventions are administration of the assessment instruments for cost effectivity analysis (see below).

**Study procedure:**

Visit 1 (Inclusion and genotyping): All eligible patients will be asked to provide written informed consent. Inclusion and exclusion criteria are checked and baseline and demographic variables will be collected (complete somatic and psychiatric history, physical examination, inventory of medication and use of drugs, and laboratory studies equivalent to the procedures in standard clinical care).

Genotyping: For eligible patients relevant genetic variants in *CYP2D6* and *CYP2C19* will be determined. These variants explain in 90-95% of the cases with changes in *CYP2D6* and *CYP2C19* enzyme activity.

Based on the drug choice and based on the latest allele definition tables (KNMP kennisbank achtergrondteksten) each patient will be classified into a metabolic phenotype category (PM,IM,EM or UM).

The time period between visits 1 and 2 will be used for washout of psychiatric drugs to which insufficient response occurred and/or that interfere with study medication (also in accordance to standard clinical procedures). Genotype information and the consequent drug dosing advice will be available within five working days after visit 1.

Visit 2: Baseline (start TCA therapy). Completion of baseline assessments of secondary clinical outcome measures. During this visit TCA treatment will be started according to the instructions per treatment strategy group (genotype guided dosing vs. dosing as usual). TCAs will be initially prescribed once daily in the evening, although the dosing regimen can later on be altered according to the patient preference. The TCAs will be prescribed and delivered by either the in-hospital or outpatient pharmacy, dependent on the situation of the patient.

Visits 3 to 9 treatment phase: During seven weeks the patients receive TCA treatment based on the dosing instructions as described above (Strategies 1 and 2). Patient assessments will take place weekly for (a) TCA concentration measurements if indicated (see description) (b) the secondary clinical outcome measures as described under visit 1 (side effects and depressive symptoms). Adherence to drug treatment will be checked weekly either by review of a drug diary kept by the patient or by interviewing the patient during visits.

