### 2.4 Sample size calculation

#### SAMPLE SIZE CALCULATION

Based on clinical guidelines and experience, we designed a survival model according to which 50% (median survival) of the control group reaches steady state concentrations within the therapeutic range at 4 weeks. We assume that 50% of the intervention group will reach steady state concentrations within the therapeutic range at a maximum of 2 weeks. This difference of only 2 weeks is a conservative estimate as patients in the intervention group may immediately start at an optimal dose based on pharmacogenetic testing results. Taking an alpha level of 5%, two-sided tests of significance and a power of 80%, the model predicts a sample size of 44 patients per group. An essential condition imposed by the subsidising party (ZonMW) was that the sample size should be enough to answer two of the secondary research questions (regarding depression scores and side effects) as well. For both of the secondary measures we need 63 patients per group based on a reduction of the mean level of side effects (Frequency, Intensity, and Burden of Side Effects Rating FIBSER (Wisniewski et al. 2006)) from 2.98 (sd=1.88) to 2.04 (based on Star-d study results) For depression scores we expect a mean HAM-D reduction in the intervention group of 17.5 (sd=9) points compared to 13 points in controls (adapted from the DUDG study Wijkstra et al. 2010). To account for drop-out before treatment initiation and loss to follow-up we aim to include 250 patients, resulting in 100 patients in each arm

The sample size calculation for this study was performed by a statistician of the Department of Health Evidence, Radboudumc ([name]).

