For reasons of efficiency of the trial we target in this study equally sized groups with specific genotypes. However for the cost-effectiveness analyses we would like to calculate expected values for the population of depressed patients incorporating the real prevalence of poor (PM), ultra (UM) and intermediate (IM) metabolizers opposed to normal metabolizers (EM). Therefore we will combine the prospectively gathered information on costs and utilities in this trial with literature on the prevalence of PM, UM and IM into a static decision analytic model. Ultimately one incremental cost-utility ratio's (ICUR) comparing genotype guided dosing with usual care, expressed as costs per QALY gained, will be calculated. The model based cost-effectiveness analysis will be carried out using probabilistic sensitivity analysis, by Monte Carlo simulation, to take all uncertainties surrounding the input parameters into account. The costs are included across a gamma distribution, the probabilities and utilities with beta distributions, which is according the guidelines of the ISPOR. The results of the 5000 simulations will be plotted in cost-effectiveness planes and in willingness to pay curves.

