### 8.1 Primary study parameter(s)

For the measurement of differences in the primary study parameter (time needed to reach a plasma level in the therapeutic range) we will report survival probabilities according to the Kaplan-Meier method together with 95% confidence intervals (CIs). Results will be compared using two-sided log-rank test statistics. Median survival times (MST) will be presented. Patients who have not reached the study endpoint after 7 weeks will be censored to the time point of their most recent plasma level assessment.

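### Because both arms wait for the genotype result, the trial cannot show any delay caused by testing, so the comparisons with usual care in the economic analyses may favour genotyping

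*Protocol*

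**What the plan says.** Under Study design (section 2, Phase 1), all patients who meet the inclusion criteria are genotyped at screening. Section 6.2 makes CYP phenotype the first stratification factor, so no patient in either arm can be randomised before the result is known.

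On timing, section 6.3 (Study procedure, Visit 1) says: "Genotype information and the consequent drug dosing advice will be available within five working days after visit 1". The sentence before it assigns the same interval to washing out earlier or interfering psychiatric drugs and describes that as standard practice. TCA treatment starts at visit 2 in both arms. The schedule table puts visit 1 at day -7 and visit 2 at day 0.

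Sections 6.1.1 and 8.1 define the primary endpoint as time to a therapeutic level but name no time zero. Section 2.4 plans for a two-week gain and comments: "This difference of only 2 weeks is a conservative estimate as patients in the intervention group may immediately start at an optimal dose".

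In the economic evaluation (section 6.3), quality of life is timed from randomisation, and the cost questionnaires are given at day 0, week 13 and week 26. The stated output is: "Ultimately one incremental cost-utility ratio's (ICUR) comparing genotype guided dosing with usual care". A budget impact analysis for national implementation follows.

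**The concern.** Dosing as usual does not need a genotype. In practice, a physician who tests first may have to wait for the result, while one who does not test can start once washout and work-up are complete. In this trial the controls wait as well, so that possible difference appears in no between-arm contrast, whether time is counted from visit 1, randomisation or first dose.

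For a comparison of dosing rules this is harmless. It matters for the incremental cost-utility ratio and the budget impact analysis, because those are meant to inform a choice between introducing testing and continuing usual care. Any days spent waiting only because of the test belong to the genotype strategy. Leaving them out can move the result in one direction only, towards genotyping.

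**Working it through.** **1. Reproduce the planned sample size.** Inputs from section 2.4: "50% (median survival) of the control group reaches steady state concentrations within the therapeutic range at 4 weeks"; "50% of the intervention group will reach steady state concentrations within the therapeutic range at a maximum of 2 weeks"; two-sided alpha 5%; power 80%. From section 8.1: "Patients who have not reached the study endpoint after 7 weeks will be censored".

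- Hazard ratio, control to genotype-guided, with exponential times: 2/4 = 0.5.
- Freedman events: (1.96 + 0.842)² × (1 + 0.5)² / (1 - 0.5)² = 7.85 × 9 = 70.6, so 71.
- Probability of an event by 7 weeks: control 1 - 2^(-7/4) = 0.703; genotype-guided 1 - 2^(-7/2) = 0.912; mean 0.807.
- Per group: 71 / 0.807 / 2 = 43.98, so 44.

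This matches the protocol: "the model predicts a sample size of 44 patients per group". The calculation is sound for time counted from first dose.

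**2. Upper bound on the delay.** Five working days span up to 7 calendar days, which agrees with day -7 to day 0 in the schedule. The assumed gain is 28 - 14 = 14 days. For a patient with no washout, no other work-up and the full turnaround, 28 v 14 days from first dose becomes 28 v 21 days from the date treatment could have started. The ratio falls from 2.0 to 28/21 = 1.33, and 7/14 = 50% of the gain is offset. For a patient whose washout or work-up lasts at least as long as the turnaround, the offset is zero.

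**3. Range between the bounds.** The protocol does not give the share s of patients whom the test would delay, so s is varied. Assumptions: a delayed patient loses the full week; controls lose nothing; times are exponential; follow-up is 7 weeks from the date treatment could have started. The median x in the genotype arm solves 2^(-x/2) × [(1 - s) + s × 2^(1/2)] = 0.5, so x = 2 + 2 × log2(1 + 0.414s). Power is for the two-sided log-rank test, from 5,000 simulated trials per row.

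| Share delayed | Median, genotype arm (weeks) | Gain over 4 weeks | Power, 100 per group | Power, 44 per group |
|---|---|---|---|---|
| 0% | 2.00 | 2.00 | 99% | 83% |
| 25% | 2.28 | 1.72 | 97% | 73% |
| 50% | 2.54 | 1.46 | 93% | 61% |
| 75% | 2.78 | 1.22 | 84% | 49% |
| 100% | 3.00 | 1.00 | 70% | 38% |

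These rows describe a test-then-treat question that the trial does not set out to answer. They show how far the answer could move. They do not show that the planned primary analysis is underpowered.

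**4. Costs and utilities.** The protocol gives no unit costs, lengths of stay or utilities, so the effect on the cost-utility ratio cannot be sized. Its direction follows from the design: an excess wait would add cost, or time in poor health, to the genotype strategy, and here both arms carry it equally.

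**The case against.** The strongest reply is that the objectives ask about dosing. Section 1 sets genotype-based dosing against dosing as usual, each with drug-level monitoring. A common start after genotyping is unbiased for that contrast, and stratification by phenotype requires it. This stands. A reader might infer that the primary result is biased towards genotyping; the documents do not support that.

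The interval also has other uses. Washout falls in it, section 2.3 restricts co-medication tightly, and section 6.3 uses laboratory and other baseline findings to settle eligibility. Many controls might not have started sooner even without the test. This stands too, and it is why the delay is a range starting at zero. A reader might take half of the gain as lost for everyone, but that is only the upper bound.

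Two further inferences fail. A reader might take the remark on starting immediately in section 2.4 to deny any wait. It concerns the dose level at treatment start, in contrast to the gradual first-week increase in Strategy 2 (section 3). A reader might also infer that care used during the wait goes unrecorded because questionnaires begin at day 0. A consumption questionnaire given that day may look back, and no recall period is stated. What can be said is that such costs cancel between arms.

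Finally, the date on which a patient could have started is partly counterfactual and would be judged by unblinded clinicians, and turnaround reflects this trial's laboratories. That is a good reason not to build the shift into the primary analysis. It is a weaker objection to a scenario in a decision model, which is already planned to replace the trial's genotype mix with real-world prevalence. The planned sensitivity and scenario analyses could take turnaround as an input, but an analysis plan cannot reliably recover dates that were never collected.

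**Conclusion.** The point holds as one about applicability and the economic comparison. The trial validly estimates the effect of genotype-guided dosing from first dose. It cannot show a delay caused by testing, because both arms wait. That delay is 0 to about 7 days per patient and would leave between 1.0 and 2.0 weeks of the assumed 2-week median gain. The lower end requires that no patient needs washout or further work-up, that the full turnaround always applies, and that usual care has no other delay. The primary analysis and the sample size need no change. The cost-utility and budget impact results against usual care could favour genotyping by an amount the protocol does not allow to be calculated. Cheap improvement.

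**What to change.** - **Record dates in the eCRF for every patient in both arms:** genotype result received, end of any washout, TCA start and, if not already captured, completion of the eligibility work-up.
- **Time zero:** state in sections 6.1.1 and 8.1 that the primary endpoint is timed from first dose, and interpret it so. In section 2.4, only clarify that the 2-week gain is counted from first dose.
- **Reporting:** give the visit 1 to visit 2 interval and the share of patients needing washout.
- **Economic scenarios:** prespecify, for the decision model and the budget impact analysis, a scenario that charges the excess wait to the genotype strategy only, in costs and utility. Excess wait = result date minus the end of washout or work-up, whichever is later, with a minimum of zero. Show it beside a zero-wait scenario that represents pre-emptive genotyping.
- **Optional:** a matching shift of the primary endpoint, labelled as a sensitivity analysis because it imputes a delay that was not observed as a difference between arms.

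The cost is a few date fields and some extra modelling. The reported advantage may become smaller. If nearly all patients need a washout as long as the turnaround, the same data will show that the wait is negligible.

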#### ECONOMIC EVALUATION (COST EFFECTIVENESS).

We aim to prospectively study cost effectiveness of the intervention during 26 weeks. This period is longer than the 7 weeks of the clinical trial, because we assume that important positive effects on patient important outcomes (quality of life and cost savings) can also be expected beyond this period.

The impact of the intervention on the quality of life of patients will be assessed both by the EuroQol 5 dimensions with 5 levels (EQ5D5L) and the SF36 at weeks 0, 2, 4, 6, 13 and 26 following randomization. Primarily, utility will be derived from the EQ5D5L as recommended by the Dutch guidelines for cost-effectiveness study. However, because SF36 seems to be more valid for this particular patient population because it includes more items within the mental health domain, utility will also be derived using the SF36 system as a secondary analysis. The derived utility will be used to estimate a Quality adjusted life year (QALY) according to the trapezium rule.

The cost analysis consists of two main parts. First, at patient level, volumes of care related to MDD and TCA therapy will be measured by means of the iMTA Medical Consumption Questionnaire. This questionnaire measures all relevant health care related costs like outpatient visits at any medical specialist and hospitalizations. In addition the medication use will be derived from the electronic patient records. Loss of productivity due to illness or recovery, will be estimated based on patient reported absences from paid (or unpaid) labor measured with the Productivity Cost Questionnaire. The iMTA Medical Consumption Questionnaire and the Productivity Cost Questionnaire will be administered at the start of the study (day 0) at week 13 and at week 26.

The second part of the cost analysis consists of determining the cost prices for each volume of consumption. The standard cost prices from the 'Dutch Guidelines for Cost Analyses' and [www.medicijnkosten.nl](http://www.medicijnkosten.nl) will be used. For units of care where no standard prices are available real costs prices will be determined on the basis of full cost pricing. Productivity losses will be

valued by means of the friction cost method. In the end volumes of care will be multiplied with the cost prices for each volume of care to calculate costs.

For reasons of efficiency of the trial we target in this study equally sized groups with specific genotypes. However for the cost-effectiveness analyses we would like to calculate expected values for the population of depressed patients incorporating the real prevalence of poor (PM), ultra (UM) and intermediate (IM) metabolizers opposed to normal metabolizers (EM). Therefore we will combine the prospectively gathered information on costs and utilities in this trial with literature on the prevalence of PM, UM and IM into a static decision analytic model. Ultimately one incremental cost-utility ratio's (ICUR) comparing genotype guided dosing with usual care, expressed as costs per QALY gained, will be calculated. The model based cost-effectiveness analysis will be carried out using probabilistic sensitivity analysis, by Monte Carlo simulation, to take all uncertainties surrounding the input parameters into account. The costs are included across a gamma distribution, the probabilities and utilities with beta distributions, which is according the guidelines of the ISPOR. The results of the 5000 simulations will be plotted in cost-effectiveness planes and in willingness to pay curves.

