#### 6.1.2 Secondary study parameters/endpoints (if applicable)

a. **Reduction of depressive symptoms after 7 weeks of treatment** (defined as the baseline HAM-D score (Hamilton 1960) minus the HAM-D score at the 7 weeks assessment.) rated by a blinded investigator and the reduction on the QIDS-SR (Rush et al. 1986) rated by the patients themselves.

b. **Highest level of side effects** based on the Antidepressant Side Effect Checklist (ASEC, Uher et al. 2009) and the FIBSER (Frequency, Intensity, and Burden of Side Effects Rating FIBSER (Wisniewski et al. 2006)) rated by the patient.

c. **Economic Evaluation:**

The impact of the intervention on the quality of life of patients will be assessed both by the EuroQol 5 dimensions with 5 levels (EQ5D5L; Lamers et al. 2005) and the The Short Form (36) Health Survey (SF36; RUG 1993) at weeks 0, 2, 4, 6, 13 and 26 following randomization.

Cost analysis: The cost analysis consists of two main parts. First, at patient level, volumes of care related to MDD and TCA therapy will be measured by means of the iMTA Medical Consumption Questionnaire. This questionnaire measures all relevant health care related costs like outpatient visits at any medical specialist and hospitalizations. In addition the medication use will be derived from the electronic patient records. Loss of productivity due to illness or recovery, will be estimated based on patient reported absences from paid (or unpaid) labour measured with the Productivity Cost Questionnaire.

The second part of the cost analysis consists of determining the cost prices for each volume of consumption. The standard cost prices from the 'Dutch Guidelines for Cost Analyses' and [www.medicijnkosten.nl](http://www.medicijnkosten.nl) will be used. For units of care where no standard prices are available real costs prices will be determined on the basis of full cost pricing. Productivity losses will be valued by means of the friction cost method. In the end volumes of care will be multiplied with the cost prices for each volume of care to calculate costs.

For more detailed information regarding the economic evaluation see the study description below (7.3).

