### 8.3 Other study parameters

For the economic analysis see also the description above (section 6.3). Here we will use a mixed repeated measures design. Missing values will be interpolated between the available assessments.

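### The QALY analysis gives week-0 utility no adjusting role, which costs precision and leaves the point ICUR dependent on chance baseline imbalance

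*Protocol*

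**What the plan says.** Protocol 6.1.2(c) and 6.3 (Economic evaluation) collect EQ5D5L and SF36 "at weeks 0, 2, 4, 6, 13 and 26 following randomization". EQ5D5L gives the primary utility and SF36 a secondary one. On the conversion to QALYs, 6.3 says: "The derived utility will be used to estimate a Quality adjusted life year (QALY) according to the trapezium rule". The horizon is set by "We aim to prospectively study cost effectiveness of the intervention during 26 weeks".

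The trial results then pass into a static decision model: "we will combine the prospectively gathered information on costs and utilities in this trial with literature on the prevalence of PM, UM and IM". Utilities enter as beta distributions, 5000 simulations are run, and the end product is stated as "Ultimately one incremental cost-utility ratio's (ICUR) comparing genotype guided dosing with usual care, expressed as costs per QALY gained, will be calculated".

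Two other places bear on adjustment. Section 8.3 says of the economic analysis: "Here we will use a mixed repeated measures design". It adds interpolation of missing values but does not say how baseline is treated or how the model relates to the QALY. Section 6.2 says "we will plan additional statistical adjustments for gender, age and sociocultural differences in case of imbalance between study groups". Utility is not on that list. For HAM-D, by contrast, 6.1.2 and 8.2 give baseline an explicit role, as a change score.

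**The concern.** A trapezium QALY that starts at week 0 counts the pre-treatment value as outcome. Its direct weight is small. But patients with higher utility at week 0 will tend to have higher utility afterwards, so a chance difference between arms at baseline carries through the whole area under the curve and into the incremental QALY, which is the denominator of the ICUR.

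The economic analysis is otherwise specified closely: instruments, QALY rule, distributions, number of simulations and handling of missing values. Someone following that text would put unadjusted utilities into the model. The remedy uses a variable that is already collected. The point matters more within metaboliser phenotypes, because 6.3 reweights phenotype-specific results to population prevalence and those cells are much smaller than a whole arm.

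**Working it through.** **Plan figures.** The protocol states no QALY gain, utility SD or baseline-to-follow-up correlation, so there is no plan figure on this point to reproduce. From the documents: assessments at weeks 0, 2, 4, 6, 13 and 26 (6.3); 100 patients per arm and an expected gain of 2 weeks in time to therapeutic level (2.4).

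**Assumptions (not in the documents).** Utility SD 0.20-0.30, the same at each visit; correlation ρ between any two visits 0.3-0.7; simple randomisation.

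**Step 1, trapezium weights.** Each visit gets half of each adjoining interval: 1, 2, 2, 4.5, 10 and 6.5 weeks, sum 26. Week 0 carries 1/26 = 3.8% of the area directly; the other visits carry 25 weeks.

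**Step 2, baseline imbalance.** One SE of the difference in mean week-0 utility is SD × √(2/100): 0.028, 0.035 and 0.042 at SD 0.20, 0.25 and 0.30.

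**Step 3, carry-over to the QALY.** Shift = imbalance × (1 + 25ρ)/52. The factor is 8.5/52 = 0.163, 13.5/52 = 0.260 and 18.5/52 = 0.356 at ρ 0.3, 0.5 and 0.7.

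| SD | ρ 0.3 | ρ 0.5 | ρ 0.7 |
|---|---|---|---|
| 0.20 | 0.0046 | 0.0073 | 0.0101 |
| 0.25 | 0.0058 | 0.0092 | 0.0126 |
| 0.30 | 0.0069 | 0.0110 | 0.0151 |

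With ρ = 0 and SD 0.25 the shift is only 0.0007, so nearly all of it is carry-over.

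**Step 4, comparators for the QALY gain (assumed).**
- A utility step reached two weeks sooner and nothing more: step × 2/52. Steps of 0.1, 0.2 and 0.3 give 0.004, 0.008 and 0.012.
- A difference that is half reached at week 2, complete at week 4 and held to week 26: the weighted weeks are 1 + 2 + 4.5 + 10 + 6.5 = 24, so 0.05 × 24/52 = 0.023 and 0.10 × 24/52 = 0.046. The central shift of 0.0092 is 40% and 20% of these.

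**Step 5, precision.** The squared weights sum to 171.5. Var(QALY) = SD² × [676ρ + 171.5(1 − ρ)]/52². At SD 0.25 and ρ 0.5 the bracket is 423.75, so the QALY SD is 0.25 × 20.59/52 = 0.0990 and the SE of the difference is 0.0990 × √0.02 = 0.0140. The correlation of QALY with baseline is 13.5/20.59 = 0.656. Adjustment multiplies the SE by √(1 − 0.656²) = 0.755.

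| ρ (SD 0.25) | correlation with baseline | SE unadjusted | SE adjusted |
|---|---|---|---|
| 0.3 | 0.47 | 0.0122 | 0.0108 |
| 0.5 | 0.66 | 0.0140 | 0.0106 |
| 0.7 | 0.81 | 0.0156 | 0.0092 |

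**Step 6, phenotype cells.** Section 6.3 speaks of equally sized genotype groups. If that means four groups of about 25 per arm (an assumption), one SE of baseline imbalance is 0.25 × √(2/25) = 0.071, and the shift at ρ 0.5 is 0.071 × 0.260 = 0.018 QALY per cell.

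**The case against.** The strongest reply is that the protocol is silent rather than wrong. The trapezium rule says how one patient's QALY is computed; it does not say that arms are compared without covariates. The mixed model in 8.3 could take in week 0 as one of its repeated assessments, and covariates are commonly left to a statistical or health-economic analysis plan, which is not at hand. This stands against any reading that the protocol rules out adjustment. It does not remove the point, because 6.2 names adjustment variables without utility and 8.3 links its model neither to the QALY nor to the simulation inputs.

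A reader might infer that the ICUR will be biased. It will not be: under randomisation the unadjusted difference is unbiased, and its SE already contains this variation. Stratifying by inpatient status (6.2) may also make the imbalance somewhat smaller than the simple-randomisation formula gives.

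A reader might infer that ordinary imbalance is as large as the QALY gain the trial can expect. That holds only if the whole gain is a two-week head start. Section 6.3 assumes that "important positive effects on patient important outcomes (quality of life and cost savings) can also be expected beyond this period", and 2.4 calls the two-week difference conservative. Against a benefit held to week 26 the shift is a fraction of the gain.

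Finally, one could turn the smaller SE into a gain in power. The protocol powers no QALY contrast and plans a simulated ICUR, so such a figure would have no anchor.

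**Conclusion.** The point holds as one of precision and specification. Followed as written, the protocol gives week-0 utility no adjusting role between the trapezium QALY and the decision model. The price is a wider QALY difference than necessary and a point ICUR that depends on the realised baseline imbalance.

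The size rests on an assumed SD and on an assumed correlation between baseline and later utility. Across the assumed range, a one-SE imbalance is of the same order as a pure two-week head start. In the central case it is roughly 20-40% of a sustained 0.05-0.10 benefit. The reduction in SE from adjustment is about 12%, 25% and 41% at correlations of 0.3, 0.5 and 0.7, and it does not depend on how long the benefit lasts. With little correlation between baseline and later utility, the matter would be negligible.

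**What to change.** In 6.3 and 8.3, state that incremental QALYs are estimated either by regressing each patient's trapezium QALY on arm, week-0 utility from the same instrument (EQ5D5L for the primary analysis, SF36 for the secondary) and the randomisation strata, or by a mixed model with a common baseline mean across arms, from which the QALY is formed with the trapezium weights.

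Include arm-by-phenotype terms. A single arm effect would average over the trial's own phenotype mix, whereas 6.3 needs phenotype-specific values to reweight to population prevalence. State that the baseline-adjusted phenotype-specific means and their standard errors, not raw arm means, feed the 5000 simulations. Say also that the model in 8.3 is the one that supplies these inputs.

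The cost is wording only. Week-0 utilities are already collected, and no patients, visits or questionnaires are added.
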